### Statistical analysis

Primary analysis will be performed on all patients included in the cohort. Only patients who withdrew consent will be excluded. Patients who decided to stop tracking or who were lost to follow-up will be included in the analysis. Any missing value will be replaced by the previous value (the last value carried forward method). Sensitivity analyses for missing values will be conducted, for example, using a multiple imputation (MICE, multiple imputation by chained equations [59]. All tests will be bilateral formulation, with a risk of type I error of 5 %.

Calculating the number of subjects required is based on the primary endpoint, i.e., the impact and the risk factors on one year all-cause mortality. The study of the literature and the completion of the preliminary inquiry (conducted in December 2009) in 14 centers that participated to the study conduct us to assume a 1-year mortality after ICU discharge of 18 %. To ensure detection with a power of 80 % of binary prognostic factors with a prevalence of 33 % and an expected OR of 1.5 and a probability of death of approximately 18 %, 1636 patients should be included in this study [60]. Assuming a rate of refusal and/or follow-up losses of 10 %, the number of patients to be included in the one-year follow-up amounts to 1800. The expected in-ICU mortality rate is 25 %. Thus, taking into account these results, the number of patients to be included is 2250.

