The primary analysis will be based on the research of the determinants of 1-year mortality of patients included in the FROG-ICU (i.e., ICU patients who needed mechanical ventilation for more than 24 h and/or treatment with a positive inotropic agent over 24 and who were discharged alive from the ICU) among clinical and biological variables and biomarkers of common interest (i.e., troponins, natriuretic peptides). The regression model used will be the logistic model. The log-linearity of the quantitative variables will be systematically evaluated, and, if appropriate, variable transformations will be performed. A selection model process will be performed using stepwise selection method. The selection process model will be further validated by bootstrap [61]. The existence of any collinearities will be observed, and a test of goodness of fit will be performed using the test and the van Cessie Houwelingen method [62]. Finally a cross-validation procedure will be performed. The measures of association will be provided, with odds ratios and confidence intervals at 95 %. An estimate of related risks will also be conducted. Finally, the overall incidence of 1-year mortality will be estimated at a confidence interval of 95 %.

As it is now recognized that highlighting the statistically significant association between new biomarkers and patient outcomes is not sufficient to demonstrate the interest of these biomarkers in terms of risk prediction [63–65]. We will use the proposed methodology of Pencina et al., which has been used in multiple articles of application. For each biomarker of interest, the net reclassification improvement (NRI) and integrated discrimination improvement (IDI) will be calculated, and comparisons between different biomarkers will be performed [64].

Regarding quality of life, a strategy similar to that outlined for the 1-year mortality analysis will be used to assess its impact and to highlight the predictors of impaired QoL at 6 months or 1 year. QoL will be estimated using the SF-36 score (ranging from 0 to 100) [66]. Altered QoL is considered when SF-36 is lower than 50. In addition, the value of the SF-36 measured in the FROG ICU study will be compared with the values that are typically found in healthy populations of the same age and sex. Interaction between quality of life and social life will be assessed by using information from the social questionnaire.

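### The attrition allowances are multiplied on rather than divided out, so 2250 inclusions at 25% ICU mortality give about 1688 ICU survivors, not the stated 1800

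*Protocol article*

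**What the plan says.** All of the figures are in the second paragraph of the protocol article's Statistical analysis section.

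- **Base size.** The design aims at "power of 80 % of binary prognostic factors with a prevalence of 33 % and an expected OR of 1.5", with "a probability of death of approximately 18 %, 1636 patients should be included in this study". The general rule on tests is "All tests will be bilateral formulation, with a risk of type I error of 5" per cent.
- **First allowance.** "Assuming a rate of refusal and/or follow-up losses of 10" per cent, "the number of patients to be included in the one-year follow-up amounts to 1800".
- **Second allowance.** "The expected in-ICU mortality rate is 25" per cent. The paragraph then concludes: "Thus, taking into account these results, the number of patients to be included is 2250".

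The next paragraph of the section limits the search for determinants of one-year mortality to patients "who were discharged alive from the ICU". The 1636 and the 1800 are therefore counts of ICU survivors, and the 2250 is a count of all inclusions. Table 2 repeats 2250 as the expected sample size.

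**The concern.** An allowance for losing a fraction d is made by dividing by (1 - d). Multiplying by (1 + d) gives too small a number, and the gap widens with d. It hardly matters at 10%, but it does at 25%.

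As written, three statements in one paragraph cannot all be true: 2250 included, 25% dying in the ICU, and 1800 entering one-year follow-up. Patients who die in the ICU cannot count towards the 1636, because the determinants analysis is confined to those discharged alive. At stake is whether the 80% power statement for the primary objective belongs to a number of patients that the stated design would produce.

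**Working it through.** **Inputs** (all from the Statistical analysis section): 1636 required for 80% power at two-sided 5%, odds ratio 1.5, one-year mortality about 18%, refusal or loss 10%, ICU mortality 25%.

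**1. Reproduce the plan's figures.**
- 1636 x 1.10 = 1799.6, stated as 1800.
- 1800 x 1.25 = 2250, as stated.

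Both match, so the method used was multiplication by (1 + d).

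**2. Divide by the retained fraction instead.**
- 1636 / 0.90 = 1817.8, so 1818 ICU survivors entering follow-up.
- 1636 / 0.90 / 0.75 = 2423.7, so 2424 inclusions, which is 174 more than 2250.
- Keeping the plan's 1800 survivors: 1800 / 0.75 = 2400 inclusions, 150 more than 2250.

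The 10% step alone differs by only 18 patients, or 1% (1818 against 1800). The ICU-mortality step carries most of the error.

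**3. Run the plan forward from 2250.**
- ICU survivors: 2250 x 0.75 = 1687.5, about 1688, against 1800 stated.
- With the full 10% spent: 1687.5 x 0.90 = 1518.75, about 1519, against 1636 required. The shortfall is 117, and 117 / 1636 = 7.2%.
- Expected deaths at 18%: 0.18 x 1519 = 273, against 0.18 x 1636 = 294.
- With no loss of vital status at all: 1688, which is above 1636.
- Break-even: 1636 / 1687.5 = 0.969, so 1636 is still met if no more than about 3% of survivors lack a one-year status.

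**4. Power, taking 1636 as the size that gives 80%.** Power = Phi((1.96 + 0.8416) x sqrt(N / 1636) - 1.96).
- N = 1519: Phi(2.8016 x 0.9636 - 1.96) = Phi(0.739) = 77%.
- N = 1688: Phi(2.8016 x 1.0158 - 1.96) = Phi(0.886) = 81%.
- Odds ratio detectable with 80% power at 1519: exp(ln 1.5 x sqrt(1636 / 1519)) = exp(0.4055 x 1.0378) = 1.52.

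**5. Sensitivity to the reading of 18%.** These are unadjusted two-group comparisons with prevalence 33% and odds ratio 1.5.
- 18% as overall mortality (about 16.0% unexposed, 22.2% exposed): the pooled formula needs 1395, and power at 1519 is 83%.
- 18% as mortality in the exposed group (12.8% unexposed): the formula needs 1653, close to 1636, and power at 1519 is 77%.

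**The case against.** The strongest reply is that 1519 is a lower end and not the plan's yield. The section says that only patients who withdrew consent are left out and that those lost to follow-up stay in the analysis. The data collection section adds that their vital status will be checked in national health records when available. Death is an outcome that such a check can recover. The number with a known status therefore lies between 1519 and 1688, and the upper end exceeds 1636. This stands, and the result has to be given as a range. It does not remove the inconsistency, because even 1688 is not 1800. Nor does keeping a patient in the analysis supply an outcome where none was recovered.

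A second reply is that 1636 may be generous. The article describes 18% as one-year mortality after ICU discharge, which reads as an overall rate. On that reading even 1519 gives about 83% in an unadjusted comparison. This also stands. The basis of 1636 is left to a cited reference, which an article may do. The 77% therefore holds only relative to 1636 as the plan's own benchmark.

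A reader might infer from the arithmetic that the study is underpowered, or that its power is simply 77%. The documents do not support that, for the two reasons above. A reader might also want to put a number on the survivors with Glasgow Outcome Scale below 4, who are not followed up. The documents give no figure for them, so only the absence of an allowance can be noted.

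It is also fair to say that the study takes all consecutive eligible patients and that Table 2 calls 2250 expected, so it need not be a ceiling. That bears on how much the error matters, not on whether the figures agree.

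**Conclusion.** The point holds as a minor correction of a stated figure. Under the plan's own 25% ICU mortality, 2250 inclusions give about 1688 survivors, and the stated 1800 would need 2400. This part rests on no reading of the 18%, on no formula behind 1636 and on no view about loss to follow-up.

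The effect on the 1636 target does depend on follow-up. It runs from a shortfall of 117 (7%), if the full 10% allowance is spent, to no shortfall, if nearly all vital status is recovered. The matching power is about 77% to 81%, on the assumption that 1636 is the size for 80%. The study population, the endpoint and the analysis are unaffected.

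**What to change.** Keep 2250 and restate the chain in the sample-size paragraph:

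- 2250 inclusions; about 1688 ICU survivors at 25% ICU mortality; about 1519 with one-year status if the full 10% is lost, and up to 1688 if vital status is recovered.
- Power of about 77%, up to about 81%, taking 1636 as the size for 80%; or, equivalently for the lower end, a detectable odds ratio of about 1.52 at 1519.
- 2424 inclusions would be needed to meet 1636 under the stated allowances.
- Survivors with Glasgow Outcome Scale below 4 at discharge are not followed up, and the chain makes no allowance for them.

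The cost is the rewording of one paragraph and, at the lower end, a slightly less favourable power statement. No extra patients and no change of design are needed.

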Here, we describe the design of the French and euRopean Outcome reGistry in Intensive Care Unit (FROG-ICU), the main objective of which is to assess the incidence and identify the risk factors of mortality during the year following discharge from the ICU. This identification of the risks will be based on the patients’ evaluations throughout their ICU stays, using clinical and “routine” biological parameters (including creatinine, sodium, potassium, hemoglobin, etc.…) as well as ICU severity score systems that are already being used to assess short-term mortality as described in Table 1. In addition, the effectiveness of novel cardiovascular biomarkers, including highly sensitive troponin, natriuretic peptides, sST2 and adrenomedullin (Table 3) to early assess adjustable factors associated with long term mortality will be evaluated.

**Table 3 Tab3:** Cardiovascular, inflammatory and renal biomarkers of potential interest in predicting long-term mortality in critically ill patients

Name	Function	Clinical interest	References
Cardio-vascular biomarkers			
copeptine	Peptide of stress deriving from vasopressine	marker of cardiovascular disease	Khan SQ, 2007
Proenkephalin	endogenous opiod polypeptide hormon	marker of cardiovascular and cerebrovascular disease	Seizinger BR, 1985
Troponin I us	part of troponin complex, heart contraction	marker of myocyte injury	Labugger R, 2000
Troponine T hs	part of troponin complex, heart contraction	marker of myocyte injury	Labugger R, 2000
Brian natriuretic peptide (BNP)	increase of natriuresis and decrease of vasculare resistance	marker of myocyte stress	Davidson NC, 1994
N-terminal pro-BNP (NT-proBNP)	biologically inactive segment of BNP	marker of myocyte stress	Moe GW, 2007
adrenomedullin (ADM)	vasodilatation, induction of angiogenesis, protection against oxydative stress and hypoxic injury	marker of myocyte stress	Khan SQ, 2007
Soluble ST2	involved in cardiac remodeling and fibrosis	marker of myocyte stress	Shah RV, 2010
galectine 3	involved in inflammation, fibrosis and neoplastic transformation	marker of heart failure	de Boer RA, 2009
Biomarkers of infection and/or inflammation			
C-reactive protrine (CRP)	acute-phase protein	marker of inflammation/infection	Elster SK, 1956
Interleukine 6	pro-inflammation and anti-inflammation cytokine	marker of inflammation/infection	Castell JV, 1990
procalcitonin (PCT)	precursor of calcitonin	marker of infection, mostly bacterial	Jones AE, 2007
Renal biomarkers			

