#### Secondary objectives

The secondary objectives of this study are: 1) to determine the incidence and the risk factors of cardiovascular morbidity and mortality in the year following an ICU stay; 2) to evaluate quality of life in the year following an ICU stay; 3) to assess the role of novel biomarkers in assessing long-term outcome after ICU discharge (Table 3).

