All patients included in the study population who survive to ICU discharge will be followed up for one additional year or until death, except for severely disabled subjects (Glasgow Outcome Scale < 4 at discharge). One-year outcome will be evaluated through data collection at 3, 6 and 12 months after ICU discharge. At those time points, patients will be contacted by telephone, and information about vital status (patient dead or alive), re-hospitalization, and cardiovascular morbidity will be recorded. For patients lost of follow-up, the vital status will eventually be checked through the national health services records when available. In addition, 4 follow-up questionnaires will be submitted to the study population: the Hospitalization Anxiety and Depression Scale (HADS) [55] and the Short Form-36 (SF-36) [56, 57] at discharge and at 3, 6, and 12 months after and the Impact of Event Scale-Revised (IES-R) [58] at 3, 6 and 12 months; a social questionnaire for assessing patients’ social environments (actual occupation, resumption of activity, level of income, marital status,…) will be submitted at 3 months after discharge.

A biological collection will be created with blood (3x10 ml in EDTA and aprotinin) and urine (10 ml) samples collected at two different time points: admission and discharge. The biological collection will allow for the measurement of novel biomarkers in a central laboratory. Table 3 lists the biomarkers with potential interest for the risk stratification of patient who survive an ICU stay.

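### The added value of the novel biomarkers rests on NRI and IDI with no internal validation tied to them, so same-data improvements would be optimistic

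*Protocol article*

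**What the plan says.** The third secondary objective is "to assess the role of novel biomarkers in assessing long-term outcome after ICU discharge". The Statistical analysis section argues that a significant association "is not sufficient to demonstrate the interest of these biomarkers in terms of risk prediction". It then states that, for every biomarker of interest, "the net reclassification improvement (NRI) and integrated discrimination improvement (IDI) will be calculated, and comparisons between different biomarkers will be performed". No other measure of incremental value is named.

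The same section says "All tests will be bilateral formulation, with a risk of type I error of 5" per cent. It gives no adjustment for the number of markers and no rule for calling a marker useful.

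Bootstrap validation and cross-validation are both planned, but they stand in the paragraph on the stepwise logistic model for one-year mortality, before NRI and IDI are introduced. Nothing links them to the biomarker step.

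The candidates are in Table 3, titled "Cardiovascular, inflammatory and renal biomarkers of potential interest in predicting long-term mortality in critically ill patients". Blood and urine are "samples collected at two different time points: admission and discharge".

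**The concern.** When a marker is added to a logistic model by maximum likelihood, its coefficient takes the sign and size that best fit the sample, even if the marker is pure noise. Predicted risks then tend to move towards the outcomes already observed. NRI and IDI count exactly that movement, so in the fitting data they lean towards improvement. Because the coefficient is estimated, their usual z-statistics also need not have the nominal null distribution.

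The article sets association aside as insufficient and puts NRI and IDI in its place, so the answer to the third secondary objective depends on them. Optimistic values would overstate what the markers add and would rank them partly by chance. The article's Discussion intends the resulting risk stratification to support a later randomised trial, so the optimism could carry forward.

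A second, separate issue is the number of candidates, each presumably tested at 5%.

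**Working it through.** The article gives no figure for the biomarker step, so there is none to reproduce. Its sample size enters only as an input. (Standard formulas with the article's assumptions give 1394 to 1466 rather than 1636. This does not matter here, because the results hardly change between the two sizes used below.)

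**Inputs from the article**
- Patients analysed: 1636 as stated, or 2250 × 0.75 × 0.90 = 1519 from its recruitment target, 25% ICU mortality and 10% losses.
- One-year mortality 18%: 0.18 × 1636 ≈ 294 deaths and 1342 survivors.
- Table 3: 9 cardiovascular + 3 inflammatory + 4 renal assays (NGAL in plasma and urine) = 16. Without the two troponins, BNP and NT-proBNP, which the primary analysis already considers, 12 remain. At two sampling times, 16 × 2 = 32.

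**Assumed, not in the article:** base-model AUC about 0.75 (varied from 0.65 to 0.80), 5 to 12 base predictors, a normally distributed marker independent of everything, and continuous (category-free) NRI.

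**Measures,** with d = risk with the marker minus risk without it
- NRI = [P(d>0) − P(d<0)] in deaths − [P(d>0) − P(d<0)] in survivors; z = NRI / √(1/deaths + 1/survivors).
- IDI = mean d in deaths − mean d in survivors; z = IDI / its two-sample standard error.

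**One noise marker, scored in the fitting data**

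| | Share positive | Rejection at nominal two-sided 5% |
|---|---|---|
| Continuous NRI | about 78-82% | about 5-7% |
| IDI | about 86-91% | about 3-4% |
| Likelihood-ratio test (n = 1519) | – | 5.4% |
| Wald test of the coefficient (n = 1636) | – | 4.6-5.2% |

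The mean NRI is about +0.042 to +0.048. The null standard error is √(1/294 + 1/1342) = 0.064, so a mean of 0.044 is 0.044/0.064 ≈ 0.7 standard errors of bias.

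**Effect of 10-fold cross-validation** (n = 1636, 400 datasets)
- Share with positive NRI falls from about 80% to 60%, and mean NRI from about 0.044 to 0.010.
- Share with positive IDI falls from about 88% to 39%.
- NRI rejection stays at about 7% (Monte Carlo standard error √(0.0675 × 0.9325/400) ≈ 1.3 points).

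Internal validation therefore removes most of the bias in the estimate, but gives no reason to rely on the NRI p-value.

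**Number of tests, kept separate.** With k independent null tests at 5%, P(at least one false positive) = 1 − 0.95^k:
- k = 12: 46%, expected number 0.6
- k = 16: 56%, expected number 0.8
- k = 32: 81%, expected number 1.6

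The simulated coefficient tests give about the same: 56% for 16 markers and 82% for 32. With correlation 0.3 among 16 markers the figure falls to 49%. So this risk would be present whichever test were chosen.

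**The case against.** The strongest reply is that the article says only that NRI and IDI are calculated and markers compared. It specifies no z-test, no cut-off and no decision rule. A reader might infer that worthless markers will be declared useful. The documents do not support that: without a rule, nothing says how a marker would be declared useful, and even under an assumed 5% rule a false positive is a probability, not a certainty.

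A reader might also infer that no multiplicity control is planned. That is silence beside a general 5% level in a condensed article on an observational cohort, and the analysis plan, which is not shown, may supply a rule.

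Nor should the 81% be blamed on NRI and IDI. It uses exactly 5% per test and would apply equally to a likelihood-ratio test. It also assumes 32 independent null tests, whereas Table 3 lists markers of potential interest only and the article does not commit to testing all of them at both times. The Background cites earlier associations with outcome for several of them, and related assays will be correlated. With one 5% test per marker, the figures are therefore upper bounds.

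The size of the bias depends on the form of NRI, which the article does not state. In the same simulations a categorical NRI was positive for only 54-57% of noise markers and its test rejected 4-5%. The IDI test is conservative, not liberal.

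The article does plan internal validation of the mortality model, and its Discussion mentions validation in a sub-cohort before any trial. Neither is linked to NRI or IDI, and the later validation is conditional and would not correct the values reported first.

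All of this limits the claim. What stands is that the only named measures of added value are optimistic in the fitting data, and that the safeguards already planned are not extended to them.

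**Conclusion.** The point holds in a limited form. It concerns a secondary objective; the primary mortality model has its own planned validation. As written, the biomarker step would give optimistic estimates if scored in the fitting data: about four in five worthless markers would show a positive continuous NRI, averaging about +0.045, and nearly nine in ten a positive IDI. These figures rest on the assumed base AUC of about 0.75, a normal marker and continuous NRI; the NRI result would be much weaker with a categorical form. The z-tests miss 5% modestly and in opposite directions, so the main fault of the chosen measures is biased estimates, not a flood of false positives.

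The 46-81% chance of at least one false positive is a separate result of the number of tests, under the assumption that all markers are null and independent. It supports reporting how many were tested; it is not evidence against NRI or IDI, nor proof that the unseen plan lacks an adjustment.

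**What to change.** Amend the biomarker paragraph as follows:

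- Fix one clinical base model in advance. Test each biomarker by the likelihood-ratio test of adding it to that model.
- Extend the bootstrap or cross-validation already planned to this step, and report the optimism-corrected change in C statistic as the measure of added value.
- State which form of NRI is used. Keep NRI and IDI as descriptive measures, split into their event and non-event parts, with bootstrap confidence intervals and no p-values.
- Report how many markers and sampling times were tested, and give a multiplicity-adjusted result beside the unadjusted one. The choice of adjustment can be left to the analysis plan.

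This needs no new data and no change to recruitment or sampling. The cost is some extra analysis work, and apparent improvements will be smaller, with fewer markers standing out after adjustment.

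### Last value carried forward, applied to SF-36 by reference, gives living non-responders an early-recovery score at 6 or 12 months and sets no stop at death

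*Protocol article*

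**What the plan says.** All of this is in the protocol article.

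- **Missing data (Statistical analysis).** The main rule is: "Any missing value will be replaced by the previous value (the last value carried forward method". It is not restricted to covariates, to one endpoint or to living patients. The section then adds: "Sensitivity analyses for missing values will be conducted, for example, using a multiple imputation".
- **Quality of life (Statistical analysis).** For predictors of impaired quality of life at 6 months or 1 year, "a strategy similar to that outlined for the 1-year mortality analysis will be used to assess its impact". The outcome is binary: "Altered QoL is considered when SF-36 is lower than 50".
- **Population of the mortality analysis (Statistical analysis).** "Primary analysis will be performed on all patients included in the cohort"; the model of determinants is then described for patients "who were discharged alive from the ICU". No separate population is given for quality of life.
- **Follow-up (Data collection and biological samples).** ICU survivors "will be followed up for one additional year or until death, except for severely disabled subjects". SF-36 is scheduled at discharge and at 3, 6 and 12 months. Vital status is collected at each contact and, for patients lost to follow-up, checked in national records when available.

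Nothing in the article says how a patient who dies before 6 or 12 months enters the quality-of-life analysis.

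**The concern.** Carry-forward needs an earlier value of the same variable. SF-36 has one by design, so the rule can act directly on a secondary outcome.

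Two groups are affected.

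1. **Living non-responders.** Their 6- or 12-month outcome becomes the score from discharge or month 3. These patients needed ventilation or inotropes for at least about a day, and a score taken that early cannot be assumed to describe quality of life up to a year later. The carried value is also treated as if it had been observed. This consequence follows from the rule as stated.
2. **Patients who die.** In the mortality analysis everyone discharged alive belongs in the model, because death is the outcome. Moved to quality of life without a stated change, that population includes people who have no quality of life to measure at 6 or 12 months. The missing-data rule, read literally, would supply a score.

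At stake is secondary objective 2. The prevalence of impaired quality of life could mix current scores, stale scores and scores of the dead. Predictors of death could then appear as predictors of poor quality of life.

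**Working it through.** **Inputs from the document.** One-year mortality after ICU discharge is 18%, refusal and/or loss to follow-up is 10%, and the sample sizes are 1636 analysable and 1800 entering follow-up (all from Statistical analysis). The article states no figure for quality of life, so there is none to reproduce. The two bases are linked by 1636 × 1.10 = 1799.6, or 1800.

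**Step 1: patients with no 12-month SF-36 because of death.**

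- 0.18 × 1636 = 294.5, about 295; alive at most 0.82 × 1636 = 1341.5, about 1342.
- 0.18 × 1800 = 324; alive at most 0.82 × 1800 = 1476.

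These are upper bounds on the number who could receive a carried score, because an earlier SF-36 must have been completed. Patients with a Glasgow Outcome Scale below 4 at discharge are not followed at all. No 6-month mortality is given, so the 6-month count cannot be computed.

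**Step 2: effect on prevalence if scores are carried past death.** Let *s* be the share below 50 among patients alive at 12 months, and *d* the share below 50 among the last scores of those who died. Assume every patient who dies has an earlier score.

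Prevalence under the rule = 0.82 *s* + 0.18 *d*; shift = 0.18 × (*d* − *s*).

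Neither *s* nor *d* is in the document. The assumed ranges are *s* = 30–50% and *d* = 50–90%:

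| *s* (alive) | *d* = 50% | *d* = 70% | *d* = 90% |
|---|---|---|---|
| 30% | 33.6% (+3.6) | 37.2% (+7.2) | 40.8% (+10.8) |
| 40% | 41.8% (+1.8) | 45.4% (+5.4) | 49.0% (+9.0) |
| 50% | 50.0% (0) | 53.6% (+3.6) | 57.2% (+7.2) |

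The shift runs from 0 to about 11 percentage points. Where it is 0 (*s* = *d* = 50%), 0.18 × 0.50 / 0.50 = 18% of those labelled as impaired are still dead, so the predictor model can be affected even when prevalence is not.

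**Step 3: living non-responders.** If a fraction *w* of living patients is missing at the time point, the shift is *w* × (share below 50 on the carried score − share below 50 on the true score). The article gives no questionnaire non-response rate. If its 10% for refusal and/or loss is borrowed as *w* (an assumption), each 10-point difference between the two shares moves prevalence by 0.10 × 0.10 = 1 percentage point. The direction depends on how patients change after the last completed form.

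**Step 4: does the planned sensitivity analysis cover this?** Multiple imputation by chained equations addresses stale scores in living non-responders, but only as a secondary check. It does not settle deaths: unless patients who have died are removed first, it too would fill in a score for them.

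**The case against.** The best counter-argument concerns deaths. A reader might infer that the plan carries SF-36 scores into patients who have died. The article does not say so. The quality-of-life strategy is called similar, not identical, and what it borrows may be only the modelling sequence. The sentence on all included patients is written for the primary analysis. Follow-up ends at death, so no SF-36 is due afterwards and an undue score need not count as missing. All of this stands: carrying past death is permitted by the wording, not declared.

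It can also be said that an article may leave the quality-of-life population to a fuller document. That would answer pure silence. Here, however, the article states a main rule, and for living non-responders that rule gives a poor result with no inference needed.

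A reader might further infer that the single cut-off of 50 makes age and sex predictors by construction. The documents do not support treating that as an error. An absolute threshold and a norm-referenced comparison answer different questions, and the article separately plans to compare SF-36 with "values that are typically found in healthy populations of the same age and sex". Replacing the outcome would be a debatable change of endpoint.

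Nor does it follow that secondary objective 2 goes unanswered, since the population comparison and the social-questionnaire analysis also serve it.

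**Conclusion.** The point holds in a limited form. The main missing-data rule, applied to SF-36, puts early scores in place of 6- and 12-month scores for living non-responders, and it contains nothing that stops it at death. The prevalence and predictors of impaired quality of life could be distorted.

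On the protocol's 18% mortality, at most about 295 of 1636 to 324 of 1800 patients are exposed to the death part at 12 months. The prevalence shift of 0 to about 11 points rests on assumed shares below 50 and on every patient who dies having an earlier score; it shows scale and is not an estimate. The size of the non-responder part cannot be fixed from the document.

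**What to change.** Add to the quality-of-life paragraph:

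- SF-36 at 6 and 12 months is analysed in patients alive at that time point.
- Multiple imputation for living non-responders is the main analysis; last value carried forward is kept only as a sensitivity analysis.
- No SF-36 score is carried or imputed past death.
- The proportion dead at each time point is reported beside the quality-of-life result.

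The cut-off of 50 and the comparison with reference populations can stay as they are.

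The cost is small. Multiple imputation is already planned as a sensitivity analysis and vital status is already collected, so no new data are needed. The 12-month analysis would rest on at most about 1342 to 1476 patients, which are the patients for whom the question has a meaning.
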